## Methods/Design

### Study design

The study is a parallel-group RCT, in which patients with type 2 diabetes, affiliated to the Belgian sickness fund Partena, were selected based on their medication consumption data, recruited by their sickness fund, and randomized to receive usual care plus The COACH Program or the usual care alone. The study will assess the difference in outcomes between the two groups. The primary outcome measure is the level of glycohemoglobin HbA1c at 6 months after randomization. The secondary outcomes are: total cholesterol (TC), low-density lipoprotein (LDL), high-density lipoprotein (HDL), triglycerides (TG), blood pressure (BP), Body Mass Index (BMI), smoking status; proportion of people at target for HbA1c, LDL-Cholesterol and Blood Pressure; self-perceived health status, diabetes-specific emotional distress, and satisfaction with diabetes care. The follow-up period is 18 months. All outcome measurements will be collected 3 times: before randomization, upon the graduation from the program (6 months after the program start); and at the end of the follow-up period (18 months after randomization). The allocation ratio is 1:1. Within-trial and modeled cost-utility analyses, - to project effects over a longer time horizon beyond the trial duration, - will be undertaken from the perspective of the health care system if the intervention is effective.

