### Patient recruitment and randomization

Patients were selected from the administrative database of the sickness fund “Partena” which belongs to the Group of the Independent Sickness Funds, based on the reimbursement data of glycaemia lowering medications in the past 12 months. Prior to the start of patient recruitment, their GP’s were informed about the study by mail. Selected patients were sent a letter of invitation to participate in the study and invited to express their interest by returning an attached response card. Those candidates who expressed their interest, or have not reacted to the invitation within two weeks, were contacted by phone. A home visit for the baseline assessment was scheduled with those patients who confirmed their participation. The assessment visit was carried out by a nurse not involved in the intervention delivery.

Randomization was performed every 2 weeks on average. To achieve a comparable HbA1c distribution within both groups, patients were stratified based on the baseline level of HbA1c: with HbA1c < 7% (53 mmol/mol), or with HbA1c ≥ 7%. Patients from both strata’s were allocated to the intervention or the control group by a data analyst of the Independent Sickness Funds, further not involved into the study, by using a random number generator programmed in Excel.

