### Statistical analysis

The two-tailed unpaired t-test will be used for continuous data and chi-square test for proportions. Where appropriate, regression analysis will be applied to account for baseline differences between the two study groups. The results will be expressed as mean (95% CI) for normal data and median (range) for skewed data. Sensitivity analysis will examine the effect of loss to follow-up on the intervention effect. The analysis will be conducted by intention to treat, which means, all patients will be followed for the full duration of the trial. Exploratory analyses will examine the effect of other factors, such as socio-demographic variables, on the outcome.

ICERs will be calculated for the mean and for the upper and lower confidence levels of marginal costs and utilities. One-way sensitivity analysis will be performed to test the relative contribution of different variables to the uncertainty around ICER and presented by means of a Tornado diagram. Probabilistic sensitivity analysis (Monte Carlo simulation) will be performed for all model inputs. The structural uncertainty will be tested through presenting different model scenarios. The results of this analysis will be presented on the cost-effectiveness plane. Probability of willingness to pay by the Belgian Health Care system will be forecasted and presented as a cost-effectiveness acceptability curve [30].

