**Figure 1 F1:**
[figure not shown]
RCT flowchart including the numbers of the enrolled and randomized patients.

**Table 2 T2:** Baseline clinical characteristics of patients in the COACH program and usual care groups

**Characteristic**	**The COACH program (n = 287)**	**Usual care (n = 287)**
Sex, no (%)		
Male	173 (60)	180 (63)
Female	114 (40)	107 (37)
Age, years		
Mean (SD)	63.8 (8.7)	62.4 (8.9)
Median (range)	65.9 (35–75)	63.9 (35–75)
HbA1c, % (mmol/mol)	7.0 (53)	7.0 (53)
Mean SD	1.1 (12)	1.0 (11)
Total cholesterol, mg/dl mean (SD)	173 (37)	178 (39)
LDL-C, mg/dl mean (SD)	93 (31)	97 (32)
HDL-C, mg/dl mean (SD)	52 (19)	51 (14)
Triglyceride, mg/dl median (range)	127 (42–1369)	130 (35–1993)
Systolic blood pressure, mmHg mean (SD)	133 (18)	132 (17)
Diastolic blood pressure, mmHg mean (SD)	75 (10)	76 (10)
BMI (kg/m2) mean (SD)	30 (5)	31 (5)
People at treatment target, no (%)		
HbA1c < 7% (53 mmol/mol)	155 (54)	159 (55)
LDL-C < 100 mg/dl	172 (60)	164 (57)
SBP < 140 mmHg	174 (61)	186 (65)
DBP < 80 mmHg	160 (56)	160 (56)
At target for all above risk factors	40 (14)	46 (16)
BMI < 25 kg/m2	33 (11)	28 (10)
In the subgroup with HbA1c ≥ 7% (53 mmol/mol)		
HbA1c, % (mmol/mol)	7.9 (63)	7.8 (62)
MeanSD	1.0 (11)	0.8 (9)
*Self-reported*		
Diagnose type 2 diabetes since, no (%)		
≤ 2 years	46 (16)	41 (14)
≥ 10 years	94 (33)	91 (32)
Smokers, no (%)	40 (14)	54 (19)
People with 1st grade relatives with known type 2 diabetes, no (%)	159 (56)	139 (49)
People with 1st grade relatives with cardiovascular disease diagnosis before 60 y.o., no (%)	93 (33)	90 (32)
With regular hypoglycemia, no (%)	26 (9)	36 (13)
People with other chronic condition(s), no (%)	211 (74)	217 (76)
Coronary heart disease	35 (12)	39 (14)
Atherosclerosis	19 (7)	9 (3)
Heart failure	21 (7)	14 (5)
Past MI	11 (4)	14 (5)
Past stroke	11 (4)	4 (1)
Past TIA	8 (3)	5 (2)
COPD	11 (4)	15 (5)
Asthma	13 (5)	19 (7)
Hypertension	111 (39)	113 (39)
Dyslipidemia	81 (28)	80 (28)
Kidney disease	17 (6)	10 (3)
Depression	19 (7)	24 (8)
Neuropathy	10 (3)	16 (6)
Having physical activity* of 30 minutes at least 5 days per week, no (%)	170 (59)	159 (55)
Having daily healthy diet**, no (%)	181 (63)	157 (55)

*Physical activity is moderate aerobic activity at 50–70% of maximum heart rate (1).

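### HbA1c at target is tested by an unstratified chi-square although its 7% cut is the randomisation stratum: a valid but inefficient analysis that can be improved at almost no cost

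*Protocol article*

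**What the plan says.** All references are to the protocol article.

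- **Outcome.** Study design lists among the secondary outcomes the "proportion of people at target for HbA1c, LDL-Cholesterol and Blood Pressure".
- **Target cut.** In Table 2, under "People at treatment target, no", the HbA1c row reads "HbA1c < 7% (53 mmol/mol". No other cut is given for this outcome.
- **Strata.** Patient recruitment and randomization says "patients were stratified based on the baseline level of HbA1c: with HbA1c < 7% (53 mmol/mol), or with HbA1c ≥ 7" (per cent). Allocation within strata was made "by using a random number generator programmed in Excel"; no blocks or other balancing device are mentioned.
- **Test.** Statistical analysis assigns "chi-square test for proportions" to binary outcomes and names no stratification factor.
- **Adjustment.** The next sentence reads "Where appropriate, regression analysis will be applied to account for baseline differences between the two study groups". It names neither the stratum nor this outcome.

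**The concern.** With the same cut for target and stratum, the stratum is baseline at-target status, which should be a strong predictor of at-target status at follow-up. A Pearson chi-square uses the total binomial variance, including the part that lies between strata. When the arms are nearly balanced on the stratum, little of that part remains in the difference between arms. The standard error is then larger than it need be and the test is conservative.

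At stake is precision in a secondary outcome close to the trial's rationale, which is that about half of patients miss their treatment targets. The primary outcome, the HbA1c level at 6 months, is not affected by this test.

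**Working it through.** **The plan's own figures.** The article gives no error rate or power for the at-target proportion, so only its sample size for mean HbA1c can be reproduced. With n per arm = 2(1.96 + 1.2816)² SD²/d²:

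- d = 0.3 and SD = 1.05 give 257.4, so 258 per arm and 516 in total, against 514 stated.
- d = 0.4 and SD = 0.94 give 116.1, so 117 per arm and 234 in total, against 232 stated.

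Both agree closely. About 258 completers per arm also follows from 574 × 0.9 / 2.

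**Inputs.** Table 2 puts 155 and 159 patients below 7%, leaving 132 and 128 at or above 7%. The stratum weights are 314/574 = 0.547 and 260/574 = 0.453. The article gives no follow-up rates and no baseline-to-follow-up correlation, so these are assumed and varied.

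**Size with balanced strata.** Let r be the within-stratum variance divided by the total variance. The true two-sided size is 2 × P(Z > 1.96/√r).

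- Assumed at-target rates of 85% (below 7% at baseline) and 25% (7% or above): overall p = 0.547 × 0.85 + 0.453 × 0.25 = 0.578. Total variance is 0.578 × 0.422 = 0.244. Within-stratum variance is 0.547 × 0.1275 + 0.453 × 0.1875 = 0.155. So r = 0.634 and the size is 1.4%.
- Assumed 75% and 35%: p = 0.569, total variance 0.245, within-stratum variance 0.206, r = 0.838, size 3.2%.

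**Power for a 10-point gain, 258 per arm, balanced strata.** Stratified power is Φ(0.10/√(2 × within/258) − 1.96). Unstratified power is Φ((0.10 − 1.96 √(2 × total/258))/√(2 × within/258)).

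- 85%/25%: 0.823 stratified, 0.665 unstratified, a loss of 16 points.
- 75%/35%: 0.707 stratified, 0.642 unstratified, a loss of 6 points.

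**Wider range, by simulation.** Stratum rates were taken from a skewed HbA1c distribution (mean 7.0, SD 1.05, 54.7% below 7%) with assumed correlations of 0.4 to 0.8 and 90% retention. The effect is the planned 0.3% shift, worth about 10.8 points at target.

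| Correlation | Rates, <7% / ≥7% | r | Size, balanced | Size, Table 2 counts | Chi-square power, balanced | Chi-square power, Table 2 counts | CMH power |
|---|---|---|---|---|---|---|---|
| 0.4 | 66.5 / 40.4 | 0.93 | 4.0% | 4.4% | 0.72 | 0.68 | 0.74 |
| 0.5 | 69.8 / 36.5 | 0.89 | 3.5% | 4.1% | 0.72 | 0.67 | 0.75 |
| 0.6 | 73.2 / 32.3 | 0.83 | 2.9% | 3.5% | 0.73 | 0.67 | 0.78 |
| 0.7 | 77.0 / 27.6 | 0.76 | 2.3% | 2.8% | 0.74 | 0.67 | 0.82 |
| 0.8 | 81.4 / 22.4 | 0.65 | 1.4% | 1.9% | 0.76 | 0.66 | 0.87 |

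The CMH test holds its size at 4.9% to 5.1% throughout. The power loss is 2 to 11 points with exact balance and 5 to 20 points at the Table 2 counts.

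The second range is larger because the small chance imbalance enters the crude comparison. COACH starts 155/287 − 159/287 = −1.4 points behind. Multiplied by the difference between stratum rates (0.26 to 0.59), this moves the crude difference by −0.4 to −0.8 points.

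**Simple randomisation within strata.** Averaged over all possible allocations, the chi-square has size 5.0%. Its power is about 0.71, still below the stratified 0.74 to 0.87.

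**The case against.** **Adjustment is already provided for.** The regression sentence directly follows the named test, so the plan cannot be read as having only an unadjusted test. That stands. But the sentence is conditional and aimed at baseline differences. For HbA1c at target these are 54% against 55%, which would hardly trigger it, and precision is the reason to use the stratum here, not imbalance.

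**The test is valid and the outcome secondary.** That also stands. Any error is conservative and creates no false positives.

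**A condensed article leaves detail to a fuller plan.** This is fair for the list of covariates. But the article does name a test for proportions, and a better one can be named in the same place.

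Three stronger readings are tempting, and the documents do not support them.

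- *The true error rate is well below 5%.* A reader might infer this from stratified allocation. It needs near-balance within strata and a strong baseline-to-follow-up link. The article states no blocking and gives no correlation. Imbalances of at most 4 in both strata would arise in about 5% of simple randomisations, which hints at forced balance but does not establish it. Conditioning on the published counts is reasonable, and gives 1.9% to 4.4%. The upper end is close to nominal.
- *A real gain would easily be missed.* At the planned shift the chi-square keeps power of 0.66 to 0.76. The loss is large only with a strong link.
- *Baseline gaps in the blood pressure and LDL targets bias those comparisons.* Systolic pressure at target is 174 against 186 of 287 (−4.2 points, z = −1.04, p = 0.30). LDL is 172 against 164 (+2.8 points, z = 0.68, p = 0.50). These are ordinary chance differences in opposite directions, and diastolic pressure is equal at 160 each. A gap would carry over in full only if baseline status fully determined follow-up status.

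**Conclusion.** The point holds as an efficiency improvement to a secondary outcome; it does not show an invalid test. The plan names an unstratified chi-square for an outcome cut at its own stratification boundary, and does not commit to adjusting for the stratum. At the Table 2 counts the conditional size is about 2% to 4%. The power lost for a gain of roughly 10 points runs from a few points to about 15 to 20.

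These figures rest on assumed correlations of 0.4 to 0.8, 10% loss spread evenly, and the Table 2 cut applying at follow-up. The direction does not depend on the exact values: stratified power was higher in every scenario examined.

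**What to change.** In Statistical analysis, name a CMH test stratified by baseline HbA1c (below 7% against 7% or above) as the analysis of HbA1c at target. Report a stratum-weighted risk difference with its 95% confidence interval. Logistic regression on arm and baseline HbA1c is an acceptable alternative.

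For the LDL and blood pressure targets, pre-specify adjustment for the baseline value. The reason is precision, and adjustment should not depend on the gaps seen in Table 2.

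This is a free improvement: a sentence or two of text and no new data, since the stratum was set at randomisation and Table 1 schedules the baseline measurements. The only downside is slightly more analysis specification.

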### Sample size

Sample size calculation was performed by using the stata software. For the subgroup of people with HbA1c ≥ 7%: assuming the difference of 0.4% between the control and intervention group (7.8% vs 7.4%) [4] and the standard deviation of 0.94% as observed within this subgroup at the baseline data analysis, we would need 232 people in both arms to achieve a power of 0.90 in this subgroup. 46% of the participants represent this group. This means that recruiting 555 people in total would be enough to power our hypothesis for the subgroup of people with HbA1c ≥ 7% at baseline if accounting for up to 10% drop-out.

For the total study population: based on the assumption that the mean difference in HbA1c between two groups will be of 0.3% (7.0% vs 6.7%) [2], and standard deviation of 1.05% - as analyzed at baseline – to achieve a power of 0.90 with alpha being 0.05, we would require 514 subjects to complete the study. Allowing for a dropout rate of up to 10%, the target recruitment number should be 566 patients totally, or 283 patients in each arm [27].

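### Intention to treat is defined as complete follow-up, which is not an analysis rule and does not fit the plan's own dropout allowance

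*Protocol article*

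**What the plan says.** The Statistical analysis section of the protocol article both names and defines the analysis principle: "The analysis will be conducted by intention to treat, which means, all patients will be followed for the full duration of the trial". The same section gives the methods:

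- Main tests: "The two-tailed unpaired t-test will be used for continuous data and chi-square test for proportions".
- Adjustment: "Where appropriate, regression analysis will be applied to account for baseline differences between the two study groups".
- Missing outcomes, mentioned only here: "Sensitivity analysis will examine the effect of loss to follow-up on the intervention effect".

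Under Study design, "The primary outcome measure is the level of glycohemoglobin HbA1c at 6 months after randomization", and "The follow-up period is 18 months". The Sample size section states that "we would require 514 subjects to complete the study" and then adds an allowance of up to 10% for dropout. No section states that all randomised patients are analysed in the arm to which they were allocated, or how a patient without a 6-month HbA1c enters the primary comparison.

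**The concern.** Intention to treat is a rule about analysis: everyone randomised is counted in the allocated arm, whatever treatment they took up. The protocol replaces that rule with an aim about follow-up. A condensed article may leave detail to a fuller document, but here the definition is given, and it is the wrong one.

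The rule matters most for patients who stop coaching or miss the 6-month visit, and the sentence does not settle how they are analysed. Only the intervention arm has coaching sessions to abandon, and Study design times the 6-month assessment at graduation from the programme. The Discussion itself links lower adherence to poorer outcome. Losses could therefore differ between arms in number or in kind. If they do, the t-test estimate is biased, and it would still be reported under the intention-to-treat label. The cost-utility analysis goes ahead only if a positive clinical difference is found, and it projects that difference over a lifetime, so the effect of any bias would not stop at the primary result.

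**Working it through.** **Does the plan expect its definition to be met?** Inputs from the Sample size section are a difference of 0.3 HbA1c points, SD 1.05, two-sided alpha 0.05 and power 0.90.

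- Per arm: n = 2 × (1.960 + 1.282)² × 1.05² / 0.3² ≈ 257.4. This rounds up to 258, or 516 in total. The stated 514 is 257 per arm, with power 0.8995, so the figure reproduces.
- Allowance for dropout: 514 × 1.10 = 565.4, which gives the stated 566. The usual form, 514 / 0.90, gives 572.
- The Patient recruitment and baseline data section reports 574 patients. With 10% loss, 574 × 0.90 ≈ 517 remain, with power about 0.90.

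The trial is thus sized to reach its power on patients who complete it, with up to about 57 of 574 lost. The allowance and the planned sensitivity analysis both show that full follow-up is not expected.

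**What does the t-test use?** An unpaired t-test on 6-month HbA1c can use only patients who have that value, unless missing values are imputed, and no imputation is mentioned. Read as written, it compares the patients with a value, by arm and without adjustment. Regression is added only at discretion.

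**How large could the bias be?** For each arm, let d be the fraction lost and δ the unseen drop-out mean minus the completer mean (positive is worse). The mean of all randomised patients in an arm is the completer mean plus d × δ. Taking the benefit as control minus intervention:

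bias (completer difference − all-randomised difference) = d_int × δ_int − d_con × δ_con

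The document gives no value for δ and no loss by arm, so every row below is an assumption.

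| Loss, intervention / control | δ, intervention / control | Bias | Share of 0.3 |
|---|---|---|---|
| 10% / 10% | 0 / 0 | 0 | 0% |
| 10% / 10% | 0.5 / 0.5 | 0 | 0% |
| 10% / 10% | 0.25 / 0 | 0.025 | 8% |
| 10% / 10% | 0.5 / 0 | 0.05 | 17% |
| 10% / 10% | 1.0 / 0 | 0.10 | 33% |
| 15% / 5% | 0.5 / 0.5 | 0.075 − 0.025 = 0.05 | 17% |
| 10% / 10% | 0 / 0.5 | −0.05 | −17% |
| 5% / 5% | 0.5 / 0 | 0.025 | 8% |

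The standard error of the difference with 257 per arm is 1.05 × √(2/257) ≈ 0.093. A bias of 0.05 is therefore about 0.54 standard errors. With no true effect, a bias of that size would raise the two-sided error rate from 5% to P(Z > 1.42) + P(Z < −2.50) ≈ 0.078 + 0.006 = 8.4%.

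**The case against.** The strongest reply is that the sentence is only a clumsy gloss. The analysis is said to be by intention to treat, the groups are defined by what patients were randomised to receive, and nothing points to an as-treated or per-protocol set. The follow-up clause also works against the feared loss, because patients who abandon coaching are still meant to be measured. Table 1 gives both arms the same HbA1c assessments, at visits separate from the coaching calls. Missing-data detail may sit in a plan that is not shown, and a sensitivity analysis for loss is already promised.

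Much of this stands. A reader might infer that the trial plans a completer analysis under an intention-to-treat label. The document does not support that. It does not restrict the t-test to patients who completed coaching or the trial, and it does not rule out imputation. Its count of completers is a sample-size figure, not an analysis set. Everyone with a 6-month value, by allocated arm and regardless of sessions received, is an available-case set.

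Nor does the document show that the effect would be overstated. The 0.5-point deficit has no source, the 10% is a ceiling for an 18-month study applied here to a 6-month endpoint, and opposite assumptions reverse the sign.

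What the reply does not remove is the definition. Aiming to follow everyone is compatible with allowing for dropout. Saying that this aim is what intention to treat means leaves the analysis rule unstated where it is needed.

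**Conclusion.** The definition is wrong as written and should be corrected before outcome data are analysed by arm. It states a follow-up aim in place of an analysis rule, and the protocol's own allowance of up to 10% dropout shows that the aim is not expected to be met in full. As written, the primary t-test is in effect an unadjusted available-case comparison, unbiased only if losses are uninformative.

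The size and direction of any bias are unknown. On the one-directional assumption that only intervention drop-outs do worse, by 0.25 to 1.0 points, with 10% lost per arm, it is 0.025 to 0.10 points. It is nil if losses are balanced and uninformative, and smaller if 6-month loss is below 10%. These figures illustrate sensitivity and are not a forecast. The point is one to fix, but it does not by itself invalidate the design.

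**What to change.** 1. Replace the sentence with: *All randomised patients are analysed in the arm to which they were allocated, regardless of the number of coaching sessions received.* Keep the commitment to follow every patient for the whole trial as a separate statement about follow-up.
2. Make the primary estimate the 6-month arm contrast from a repeated-measures mixed model with HbA1c at baseline, 6 and 18 months, arm by visit, and the randomisation stratum. Randomisation was stratified on baseline HbA1c, so every randomised patient has at least that value and can enter the model. The estimate is valid if data are missing at random. It does not remove bias when drop-outs differ in ways the observed values do not capture.
3. To cover that case, specify the sensitivity analysis already promised as multiple imputation with a delta shift on missing HbA1c. Vary delta separately in each arm, in both directions, up to the point where the conclusion changes.

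The cost is revised wording and somewhat more analysis work. All three visits are already in Table 1, so no new data are needed, and the stated 514 and 566 do not change.

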### Cost-utility analysis

Cost-utility analysis will be performed if the clinical study demonstrates a positive difference in clinical end points between two study groups [28,29]. Within-trial and modeled cost-utility analyses will be undertaken from the perspective of the health care system, i.e. taking into account direct health care costs to the system including both the cost for the health insurance as the patient out-of pocket costs [30].

The incremental cost-effectiveness ratio (ICER) will be calculated by using the following equation: ICER = ∆Costs/∆QALYs, where ∆Costs is the difference between the mean total cost in the intervention and the control group and ∆QALY is the area between two curves depicting the evolution of the means in QALYs-utilities over time in the intervention and the control group.

Modeling will be applied for projecting effects observed within the trial over a life-time horizon. The assumptions on the progression of type 2 diabetes depending on the known intermediate surrogate outcomes and the associated health status will be derived from published sources. The model’s outcomes validity will be tested through critical appraisal by experts. Future costs of type 2 diabetes without complications, and costs associated with each fatal or non-fatal diabetes-related complication will be estimated based on the epidemiological data available in Belgium and the database of the Independent Sickness Funds. Future costs will be discounted at 3%, future QALYs gained at 1.5% per annum [30]. ICERs will be calculated at various time horizons (e.g., 2, 5, 10, 20 years) [30].

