### Within trial costs and health utilities analysis

Information on the utilization of healthcare services will be obtained from the database of the Independent Sickness Funds. The health care services include primary care visits, visits to emergency departments, visits to specialists, hospital stays, medications, laboratory tests, imaging techniques, paramedical care and other therapies. Out-of-pocket costs will be derived from the published reimbursement regulations. All cost items described above will be specified and expressed in physical, and in monetary units (Euro’s). As baseline measure of costs in both groups, the costs of health care consumption in the 12 months period prior to the trial will be taken. Diabetes – and non-diabetes related costs will be distinguished. Costs imposed by the study that are not part of the routine practice, such as protocol-driven nurse assessment visits and laboratory tests, will not be included into the cost analysis.

The health utility weights will be derived from the Flemish utility value system based on the EQ-5D scores obtained during the assessments visits [30]. QALYs associated with the future diabetes complications will be derived from published sources. QALYs will be calculated assuming linear interpolation between measurement points and calculating the area under the curve, to give a number of QALY gained per patient over the trial period [29].

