However, a number of design limitations need to be mentioned. 1) The research setting will to a certain extent affect the study results. Several elements of the protocol are not part of the usual care, e.g. home visits for the purpose of the data collection including the additional laboratory analysis. 2) In the within trial cost-utility analysis, incremental QALYs is one of the primary endpoints of the economic evaluation but can only be derived from a number of generic health surveys with a limited capacity in detecting minor differences in health status, at least in the short term. The disease specific questionnaires have shown to be more sensitive and relevant for use in certain interventions and patient groups. In the last years, researchers have been developing algorithms to translate the scores obtained from disease specific health status questionnaires into health utility weights. However the performance of these algorithms have been criticized [32]. Further research in health-economics should focus on development of cross-cultural instruments capable of capturing common measures of well-being with a higher grade of sensitivity to minor condition divergences.

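### The planned ICER range, built from separate confidence limits for costs and utilities, has no defined coverage, and the QALY difference has no assured adjustment for baseline utility

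*Protocol article*

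**What the plan says.** The Cost-utility analysis section defines the ICER as incremental cost over incremental QALYs. For the numerator, "Costs is the difference between the mean total cost in the intervention and the control group". For the denominator, "QALY is the area between two curves depicting the evolution of the means in QALYs-utilities over time in the intervention and the control group". Within trial costs and health utilities analysis adds that "QALYs will be calculated assuming linear interpolation between measurement points and calculating the area under the curve", giving a QALY figure for each patient. It also takes health care costs over the 12 months before the trial as the baseline cost measure in both groups.

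On uncertainty, the Statistical analysis section states that "ICERs will be calculated for the mean and for the upper and lower confidence levels of marginal costs and utilities". It then lists a one-way analysis shown as a Tornado diagram, a Monte Carlo analysis of the model's inputs, scenario analyses, a cost-effectiveness plane and an acceptability curve. On baseline differences, the same section says: "Where appropriate, regression analysis will be applied to account for baseline differences between the two study groups".

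The Discussion warns that incremental QALYs can come only from "generic health surveys with a limited capacity in detecting minor differences in health status", at least in the short term.

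**The concern.** The quoted rule fixes a method. It takes the confidence limits of incremental cost and of incremental utility, each found separately, and forms ratios from them. Three things are wrong with that.

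- The limits of a ratio depend on the joint distribution of numerator and denominator. Marginal limits discard the covariance, and the text does not say which cost limit goes with which QALY limit.
- A ratio is unstable when its denominator may be zero. The Discussion's own remark on generic instruments makes a QALY interval that reaches zero plausible. The ratio can then turn negative, and a negative ICER does not distinguish a dominant programme from a dominated one.
- The tools that could show joint uncertainty are tied to the inputs of the model. It is not clear that they cover sampling uncertainty within the trial. Nor is it clear whether the confidence-limit sentence concerns the within-trial ICER, the modelled ICER or both.

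A second, smaller point is that the QALY difference is written as the area between two mean curves that start at baseline. A chance difference in baseline utility therefore enters the result unless someone decides to adjust for it.

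At stake is the reading of the economic evaluation, which is the third aim and is meant to inform reimbursement.

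**Working it through.** The documents give no cost, utility, SD or correlation, so there is no ICER figure of the plan's own to reproduce. The HbA1c sample size is not involved. From the documents I take visits at 0, 6 and 18 months (Study design and Table 1), linear interpolation with area under the curve, and 287 patients per arm (Table 2). Everything else below is assumed.

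**1. One example.** Assume incremental cost 300 (SE 250) and incremental QALYs 0.020 (SE 0.015).

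- Point ICER: 300 / 0.020 = 15,000.
- Cost limits: 300 ± 1.96 × 250 = −190 and 790.
- QALY limits: 0.020 ± 1.96 × 0.015 = −0.0094 and 0.0494.

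| Pairing | Ratio |
|---|---|
| upper cost / upper QALY | 790 / 0.0494 = 15,992 |
| lower cost / lower QALY | −190 / −0.0094 = 20,213 |
| upper cost / lower QALY | 790 / −0.0094 = −84,043 |
| lower cost / upper QALY | −190 / 0.0494 = −3,846 |

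With like limits paired, both results lie above the point estimate, and the one from the lower limits is the larger. It also describes a programme that is cheaper and worse, so its positive sign does not mean what the other positive sign means. With opposite limits paired, both results are negative: the first is dearer and worse, the second cheaper and better.

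**2. Coverage.** Bivariate normal estimates were simulated (400,000 draws per setting, cost-QALY correlation −0.5, 0 and 0.5). The range was taken as the span between the two ratios.

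| Assumed cost (SE), QALY (SE) | True ICER | Like limits paired | Opposite limits paired | Lower QALY limit below 0 |
|---|---|---|---|---|
| 500 (150), 0.030 (0.008) | 16,667 | 14–21% | about 96% | about 4% |
| 500 (150), 0.030 (0.015) | 16,667 | about 51% | about 52% | about 48% |
| 500 (300), 0.030 (0.015) | 16,667 | about 49% | about 52% | about 48% |
| 500 (300), 0.020 (0.020) | 25,000 | 31–42% | about 17% | about 83% |

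In the first row, at the true values, like pairing gives 206 / 0.01432 = 14,385 to 794 / 0.04568 = 17,382. Opposite pairing gives 206 / 0.04568 = 4,510 to 794 / 0.01432 = 55,447. Coverage thus depends on the unstated pairing and on QALY precision.

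**3. Baseline utility in the QALY difference.** With u0, u6 and u18 the utilities at the three visits,

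QALY = 0.5 × (u0 + u6)/2 + 1.0 × (u6 + u18)/2 = 0.25 u0 + 0.75 u6 + 0.50 u18 (weights sum to 1.5 years).

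If the three utilities share one SD and one pairwise correlation r, a chance baseline gap d shifts the unadjusted QALY difference by d × (0.25 + 1.25 r). For d = 0.02 this is 0.005 (r = 0), 0.0175 (r = 0.5), 0.0225 (r = 0.7) and 0.030 (r = 1). With an assumed utility SD of 0.15 to 0.25, the chance SE of d is SD × √(2/287), or 0.0125 to 0.0209.

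**4. Precision.** In units of the squared SD:

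- Raw QALY variance is 0.25² + 0.75² + 0.50² + 2r(0.1875 + 0.125 + 0.375) = 0.875 + 1.375 r.
- Adjusting for u0 removes (0.25 + 1.25 r)².
- At r = 0.5: raw 1.5625, adjusted 1.5625 − 0.7656 = 0.7969, ratio 0.51.
- At r = 0.7: raw 1.8375, adjusted 1.8375 − 1.2656 = 0.5719, ratio 0.31.

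For r from 0.5 to 0.7 and no dropout, the unadjusted SE of the QALY difference runs from 0.0125 × √1.5625 = 0.016 to 0.0209 × √1.8375 = 0.028. The adjusted SE runs from 0.0125 × √0.5719 = 0.009 to 0.0209 × √0.7969 = 0.019. The SE of 0.015 in step 1 and in the middle rows of step 2 is therefore slightly kinder than these assumptions give an unadjusted analysis.

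**The case against.** The case for the plan has substance.

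- **The range is not called a confidence interval.** Next to the Tornado diagram it could be read as a deterministic range. It would then be wrong to say that the protocol reports an invalid interval as a valid one. That much stands. But values computed at confidence limits will be read as an interval, and as a deterministic range they still cannot be interpreted when the QALY limit crosses zero.
- **A plane and an acceptability curve are already planned.** True, and the fix should use them. Their stated source is the Monte Carlo analysis of model inputs, so their reach into the within-trial result is unclear rather than shown to be absent.
- **Adjustment is not excluded.** A reader might infer that the QALY curves will certainly go unadjusted. The documents do not support that: the regression clause could cover utilities and costs, pre-trial costs are collected, and QALYs are already worked out per patient. What remains is that the clause names neither outcome and leaves the decision open, while the written definition of the QALY difference has no such term.
- **No imbalance is shown.** Table 2 reports no EQ-5D utility. A reader might infer bias, but under 1:1 randomisation a baseline gap is chance error.
- **The stakes are bounded.** The cost-utility analysis goes ahead only after a favourable clinical result, and the Discussion ties reimbursement to the lifetime analysis. That limits severity. It does not remove the point, because a within-trial analysis is planned in its own right and the model projects effects observed in the trial.

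**Conclusion.** The confidence-limit rule for the ICER is wrong as written. That conclusion is algebraic: ratios of marginal limits ignore covariance, the pairing is open, and the result breaks down as the QALY limit nears zero. How badly it would perform here cannot be established. The simulated coverage of 14% to 96% and the example ratios rest on assumed costs, QALYs and standard errors.

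The baseline adjustment is a free improvement, not an error. Under a common correlation of 0.5 to 0.7, adjusting for baseline utility would cut the variance of the QALY difference by 49% to 69%. It would also stop a chance gap from passing into the ICER. Neither a real gap nor its size can be shown from the documents.

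Overall severity is moderate. The HbA1c primary outcome, its sample size and the conduct of the trial are unaffected.

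**What to change.** For the within-trial analysis:

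1. Delete the ICERs at the confidence limits of costs and utilities, and state which ICER each remaining uncertainty analysis concerns.
2. Estimate incremental QALYs by regression of per-patient QALYs on arm, baseline EQ-5D utility and HbA1c stratum. Estimate incremental cost by regression of per-patient cost on arm and prior-12-month cost. Fix both in advance rather than where judged appropriate.
3. Obtain joint uncertainty by resampling patients within arm, keeping each patient's cost and QALY together and refitting both regressions in each resample. Fieller limits or incremental net benefit would also serve. For a willingness to pay λ, net benefit is λ × ΔQALY − ΔCost, with variance λ² Var(ΔQALY) + Var(ΔCost) − 2λ Cov(ΔQALY, ΔCost), so the covariance is used.
4. Show these results on the cost-effectiveness plane and acceptability curve already planned, kept apart from the model-based probabilistic analysis.

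The cost is plan wording and analysis programming. Baseline EQ-5D, the HbA1c stratum and pre-trial costs are already in the data collection, so no new data and no change to trial conduct are needed.
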